#### Psychosocial outcomes

All psychosocial measures are exploratory. We will include the Adverse Childhood Experiences International Questionnaire (ACE-IQ) [64] and the Coping Self-Efficacy (CSE) [65] scale as exploratory psychosocial measures. The ACE-IQ assesses exposure to early life adversity, providing context for participants’ mental health needs and potential barriers to care. The CSE scale measures perceived ability to cope with stress through problem-solving, emotional regulation, and social support. Lastly, we will be measuring social support using the 3-item Oslo social support scale (OSSS-3) [66], which measure the number of close confidants, perceived concern from others, and ease of obtaining practical help. Together, these tools will help us explore how early adversity and coping capacity may influence engagement with the intervention and inform future trauma- and resilience-informed adaptations.

### Power analysis

This RCT is powered only to detect intervention effects on symptoms of CMDs, as measured by the SSQ-14, which is the primary outcome. All other quantitative outcomes—including other mental health measures, HIV engagement indicators, and psychosocial variables—will be treated as exploratory and used to inform effect size estimates and future trial design. With the proposed sample size of 126 participants (63 per arm) and using a two-sided alpha level of 0.05, the study will have 80% power to detect a medium effect size of Cohen’s *d* = 0.5 in SSQ-14 scores, which will be analyzed as a continuous outcome. This is a conservative estimate, selected to reflect a clinically meaningful but smaller effect than that observed in the original Friendship Bench trial, which reported a large effect (*d* ≈ 0.75–0.8) over a 6-month period. Accounting for 30% attrition, the sample size estimate was adjusted to account for an original sample size of 180 participants (90 per group). Since our study primarily measures outcomes at 3 months, a smaller effect size is assumed to avoid overestimating power. Between-group comparisons will be conducted at the 3-month follow-up, prior to the waitlist control group receiving the intervention. At 6 months, only within-group analyses will be conducted to assess sustained changes in the intervention group and pre-post change in the waitlist control group. No between-group comparisons will be performed at 6 months.

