## Methods

### Study design

We will conduct a two-arm HT1 randomized controlled trial (RCT) to evaluate the effectiveness and implementation of the adapted Friendship Bench intervention, *Mpata Yathu*, on HIV prevention and treatment, and depression outcomes among young women living with or at risk for HIV, with a lifetime history of GBV and depression symptoms in Zambia. This study will have two arms: an intervention group and a waitlist control group. This trial follows a superiority framework, testing whether the intervention improves outcomes compared with the waitlist control group. The SPIRIT figure [51] (Fig. 2; see Additional file 3 for Checklist) illustrates the timeline of enrollment, intervention, assessments, and close-out procedures for the RCT of the *Mpata Yathu* counseling intervention for AGYW exposed to GBV in Zambia. All items from the WHO Trial Registration Data Set are provided in Additional file 1. The intervention is designed to be delivered in six sessions, with one session per week. However, participants will be given up to 3 months to complete all sessions to accommodate common barriers such as caregiving responsibilities, stigma, mobility, and illness [52–55]. Counseling sessions will be scheduled to accommodate participant availability, and lay counselors will track session completion. After screening and enrollment, eligible participants will be randomized in a 1:1 ratio to either group.*Intervention group:* Participants will receive up to six individual counseling sessions between baseline and 3-month follow-up (0–3 months).*Waitlist control group:* Participants will receive usual care from 0 to 3 months, followed by the intervention (up to six counseling sessions) between 3 and 6 months.

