### Study outcomes

All outcomes will be assessed at both 3-month and 6-month follow-up timepoints. The 3-month follow-up will serve as the primary endpoint for between-group comparisons (intervention vs. waitlist control). At the 6-month follow-up, only within-group changes will be assessed, as both groups will have received the intervention by this time. The waitlist control group will begin intervention delivery after completing the 3-month assessment, with no contamination expected due to the ± 1 month window applied to the time in which follow-up assessments must be completed. We outline all quantitative study outcomes with their corresponding measures and timepoints in Table 1. Table 2 outlines the HIV prevention and engagement outcomes, which are reported separately since outcome measures differ based on seropositivity status. Table 3 describes the qualitative measures, which are all implementation process measures. All instruments will be translated from English to Nyanja and Bemba using a forward–backward translation process to ensure linguistic and cultural equivalence.

**Table 1 Tab1:** Quantitative outcomes, measures, and data collection timeline (excluding HIV outcomes)

Outcome	Measure or data source	Data collection time points		
		Baseline/pre-intervention	3-month follow-up	6-month follow-up

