### Quantitative data analysis

We will use descriptive statistics to summarize participant characteristics at baseline, feasibility and acceptability metrics, and other implementation outcomes. To assess baseline differences between participants who complete the intervention and those who drop out, we will conduct bivariate comparisons using independent samples t-tests or Wilcoxon rank-sum tests for continuous variables and chi-square or Fisher’s exact tests for categorical variables.

*Primary outcome analysis (powered):* To assess the effect of the adapted intervention on symptoms of CMDs (SSQ-14), we will use mixed-effects linear regression models. This is the only outcome for which the study is statistically powered, based on detecting a standardized mean difference of Cohen’s d = 0.5 at the 3-month follow-up. The model will include:A random intercept for participants to account for within-subject correlation from repeated measures;A fixed effect for time (baseline vs. follow-up);A fixed effect for study group (immediate intervention vs. delayed control);A group × time interaction term to estimate the differential intervention effect over time.

If the model assumptions (e.g., homoscedasticity, normally distributed residuals) are not met, we will consider using generalized linear mixed models with appropriate link functions and distributional assumptions to reduce the risk of Type I and Type II errors.

*Exploratory analyses:* All other outcomes will be analyzed using mixed-effects linear, logistic, or ordinal regression models, depending on the outcome type. These outcomes include:Mental health outcomes: depression (PHQ-9; binary and continuous), anxiety (GAD-7; continuous), and PTSD (CPSS; continuous) symptoms;HIV prevention outcomes (among HIV-negative or status-unknown participants): consistent condom use, PrEP uptake or readiness, HIV risk behaviors (via WAF), and HIV prevention self-efficacy/readiness (via HPRM);HIV treatment outcomes (among HIV-positive participants): ART adherence, clinic attendance, viral load documentation (if available), and HIV treatment self-efficacy (via HIV-SE);

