*Moderation and mediation analyses (exploratory)*: Post hoc exploratory analyses will assess whether changes in mental health outcomes mediate or moderate the intervention’s effects on HIV-related outcomes. Mental health change scores will be calculated separately for each follow-up period (i.e., 3 months and 6 months post-intervention) by subtracting baseline values from the respective follow-up values. This will allow us to assess both short-term and sustained mental health changes and explore their relationship with HIV-related outcomes over time.Mediation: We will test whether changes in CMD symptoms (SSQ-14), depression (PHQ-9), anxiety (GAD-7), or PTSD (CPSS) symptoms help explain (mediate) observed changes in HIV prevention or treatment outcomes using causal mediation models.Moderation: We will include interaction terms between changes in mental health symptoms and intervention group to assess whether the impact of the intervention on HIV outcomes differs depending on mental health changes. Additionally, we will explore whether baseline levels of early adversity (measured by the Adverse Childhood Experiences International Questionnaire; ACE-IQ) [64], social support (measured by the Oslo social support scale; OSSS-3) [66], and coping self-efficacy (measured by the Coping Self-Efficacy scale; CSE) [65] moderate the relationship between the intervention and mental health or HIV outcomes.

*Adjustment variables and stratified analyses:* HIV status (positive vs. negative/unknown) will be included as a covariate in pooled models to adjust for baseline differences. Stratified analyses by HIV status will be considered if each group has a sufficient sample size to support reliable subgroup modeling (e.g., ≥ 40 participants per group). Given the small overall sample size (*N* = 90, accounting for 30% attrition), such stratified analyses may be underpowered and are therefore considered exploratory and hypothesis-generating only. All models will follow an intention-to-treat (ITT) framework, and statistical significance will be assessed at a two-sided *α* = 0.05, with 95% confidence intervals reported. Non-adherence will be handled by analyzing all participants as randomized (ITT); we will also run a pre-specified per-protocol sensitivity analysis defined as completion of ≥ 4/6 sessions and no major protocol deviations. Missing data will be addressed using mixed-effects models, which provide valid estimates under missing-at-random assumptions.

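### The waitlist arm's 6-month pre-post change has no stated starting visit, and every reference point the article gives leads to baseline, three months before that arm is treated

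*Protocol article*

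**What the plan says.** The design is clear about when the waitlist arm is treated. Under Study design, these women have usual care in months 0 to 3, "followed by the intervention (up to six counseling sessions) between 3 and 6 months". Under Study outcomes, "The waitlist control group will begin intervention delivery after completing the 3-month assessment".

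The 6-month analysis is within-arm only: "At the 6-month follow-up, only within-group changes will be assessed, as both groups will have received the intervention by this time". The Power analysis section repeats this and gives its purpose as "to assess sustained changes in the intervention group and pre-post change in the waitlist control group". Neither place names the visit from which the waitlist change is measured.

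Reference visits are named elsewhere:

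- Table 1 heads its first visit column "Baseline/pre-intervention", for both arms.
- The primary model in Quantitative data analysis includes "A fixed effect for time (baseline vs. follow-up"), a two-level time term.
- The paragraph on moderation and mediation states: "Mental health change scores will be calculated separately for each follow-up period (i.e., 3 months and 6 months post-intervention"), formed "by subtracting baseline values from the respective follow-up values". It makes no distinction between arms. The HIV outcomes section also describes its 3- and 6-month visits as post-intervention.

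**The concern.** For the waitlist arm, baseline is not the pre-treatment visit and month 3 is not a post-treatment visit. If the 6-month pre-post change is taken from baseline, it spans three months of usual care as well as the months in which sessions were offered. Women are enrolled because a symptom score is raised (SSQ-14 of 9 or more, or PHQ-9 of 10 to 14), so some fall on re-measurement is expected without treatment. That fall would be reported as part of the change over the intervention.

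There is no between-group comparison at 6 months, so the starting visit decides what the waitlist result means. The explicit baseline subtraction also carries the untreated months into the waitlist arm's 6-month change scores for mediation and moderation.

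**Working it through.** **1. The plan's own figure.** For d = 0.5, two-sided alpha 0.05 and 80% power, n per arm = 2(1.960 + 0.842)² / 0.5² = 62.8, so 63. Power at 63 per arm is 0.801 by the normal formula and 0.795 by the t distribution. Allowing for 30% attrition, 63 / 0.70 = 90 per arm, or 180 in all. The stated 63 and 90 reproduce. Both concern the 3-month between-group comparison, and neither depends on the starting visit for the waitlist change. The article states no figure for the 6-month within-group analysis.

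**2. What each starting visit measures.** In the waitlist arm:

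(month 6 − month 0) = (month 3 − month 0) + (month 6 − month 3)

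The first term on the right is untreated change; the second covers the treated period. A baseline start reports the sum. A month 3 start reports the second term alone. The symptom scales are collected at all three visits (Table 1), so both terms can be computed.

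**3. Which start the article's rules lead to.**

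- Table 1 label: baseline counts as pre-intervention for both arms.
- Primary model: with time coded at two levels, months 3 and 6 are not separate levels, so a month 3 to month 6 contrast cannot be estimated from that term.
- Change scores: baseline is subtracted at both follow-ups in both arms.
- Study design and Study outcomes: the waitlist arm's last untreated value is at month 3.

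The first three point to baseline. The last shows why that does not fit this arm.

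**4. Possible size of the untreated part (illustration).** The documents give no SD, correlation between visits, or share of screened women above the cutoff, so all are assumed. For selection above a cutoff c exceeded by a share p of a normal population, expected regression to the mean in population SD units is (1 − ρ) × φ(c) / p, where ρ is the correlation between visits. The factor φ(c) / p is 1.40 at p = 20%, 1.16 at 30% and 0.80 at 50%.

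| Share above cutoff | ρ = 0.5 | ρ = 0.7 | ρ = 0.9 |
|---|---|---|---|
| 20% | 0.70 | 0.42 | 0.14 |
| 30% | 0.58 | 0.35 | 0.12 |
| 50% | 0.40 | 0.24 | 0.08 |

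The range is 0.08 to 0.70 SD. The trial's design effect is 0.5, although the two SDs need not be equal: one belongs to the screened population, the other to enrolled women.

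**5. What that could do to a within-arm test.** Take n = 63, no treatment effect, and an untreated improvement D in SD units of enrolled women, with equal SDs at both visits. The standard error is √(2(1 − r)/63), where r is the correlation between the two visits: 0.126 at r = 0.5 and 0.098 at r = 0.7. The probability that a two-sided paired z-test from baseline is significant at 0.05 is:

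| D | r = 0.5 | r = 0.7 |
|---|---|---|
| 0.1 | 0.13 | 0.18 |
| 0.2 | 0.36 | 0.54 |
| 0.3 | 0.66 | 0.87 |

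**The case against.** The strongest reply is that no sentence says the waitlist pre-post change starts at baseline. For an arm treated in months 3 to 6, pre-post can naturally mean month 3 to month 6, and the use of different terms for the two arms suggests that different contrasts were intended. The baseline subtraction belongs by name to the exploratory mediation and moderation analyses. The two-level time term belongs to a model whose target is the 3-month comparison, where two levels are enough. A column label does not define a contrast, and an article may leave the starting visit of an unpowered within-arm analysis to the analysis plan.

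Much of this stands. A reader might infer that the plan fixes the waitlist change at baseline; the text does not support that. What remains is more than missing detail. The pre- and post-intervention labels are wrong for the waitlist arm, the change-score rule subtracts baseline at 6 months without separating arms, and the only stated time coding cannot give a month 3 to month 6 contrast. An analysis plan that followed this text would arrive at baseline.

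The size is also open to challenge, rightly. Women may enter on PHQ-9 alone with an SSQ-14 below 9, and those with PHQ-9 or GAD-7 above 14 are excluded. Both would tend to reduce regression to the mean on the SSQ-14, as would measuring the baseline SSQ-14 afresh after screening.

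**Conclusion.** The point holds as an unstated starting visit that the article's own labels and rules would resolve to baseline, contrary to its own treatment schedule for the waitlist arm. A baseline start would mix untreated drift and regression to the mean into that arm's 6-month result. The amount is unknown: about 0.1 to 0.7 SD from regression to the mean under assumed correlations of 0.5 to 0.9 and 20 to 50% of screened women above the cutoff, and probably less given the entry and exclusion rules.

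Three stronger readings go beyond the documents. A reader might infer that a large, highly significant waitlist change would appear even if the intervention did nothing; with an untreated improvement of 0.2 SD the probability of significance is only 0.36 to 0.54, and every input is assumed. A reader might infer that the sponsor means to present the waitlist change as replication of the effect; no sentence says so. A reader might infer that the primary result is compromised; the between-group comparison is set at 3 months, before the waitlist arm is treated, so neither it nor the sample size is affected.

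**What to change.** - Code time at three levels (0, 3 and 6 months) in the model used for the within-arm changes.
- Define the waitlist pre-post change as month 6 minus month 3, and report the same women's month 0 to 3 change beside it as untreated change.
- For sustained change in the intervention arm, report month 3 to month 6, alongside change from baseline if wished.
- Correct the pre-intervention label in Table 1 and the post-intervention label in the moderation and mediation paragraph for the waitlist arm, and restate the baseline-subtraction rule so that it fits that arm's schedule.
- State that 6-month within-arm changes are uncontrolled and support no efficacy claim.

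The cost is some wording and one added contrast, on data already planned for collection; the sample size does not change. The downsides are that the waitlist change will probably look smaller, and that the month 3 to 6 change, though it excludes the months known to be untreated, is still uncontrolled.

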### Quantitative data analysis

We will use descriptive statistics to summarize participant characteristics at baseline, feasibility and acceptability metrics, and other implementation outcomes. To assess baseline differences between participants who complete the intervention and those who drop out, we will conduct bivariate comparisons using independent samples t-tests or Wilcoxon rank-sum tests for continuous variables and chi-square or Fisher’s exact tests for categorical variables.

*Primary outcome analysis (powered):* To assess the effect of the adapted intervention on symptoms of CMDs (SSQ-14), we will use mixed-effects linear regression models. This is the only outcome for which the study is statistically powered, based on detecting a standardized mean difference of Cohen’s d = 0.5 at the 3-month follow-up. The model will include:A random intercept for participants to account for within-subject correlation from repeated measures;A fixed effect for time (baseline vs. follow-up);A fixed effect for study group (immediate intervention vs. delayed control);A group × time interaction term to estimate the differential intervention effect over time.

If the model assumptions (e.g., homoscedasticity, normally distributed residuals) are not met, we will consider using generalized linear mixed models with appropriate link functions and distributional assumptions to reduce the risk of Type I and Type II errors.

*Exploratory analyses:* All other outcomes will be analyzed using mixed-effects linear, logistic, or ordinal regression models, depending on the outcome type. These outcomes include:Mental health outcomes: depression (PHQ-9; binary and continuous), anxiety (GAD-7; continuous), and PTSD (CPSS; continuous) symptoms;HIV prevention outcomes (among HIV-negative or status-unknown participants): consistent condom use, PrEP uptake or readiness, HIV risk behaviors (via WAF), and HIV prevention self-efficacy/readiness (via HPRM);HIV treatment outcomes (among HIV-positive participants): ART adherence, clinic attendance, viral load documentation (if available), and HIV treatment self-efficacy (via HIV-SE);

*Composite HIV engagement scores*: To simplify analysis and reflect multiple components of HIV prevention and treatment engagement, we will construct composite engagement scores for each group (based on HIV status). Composite scores will be created by assigning a binary value (e.g., 0 = no, 1 = yes) to multiple related indicators of HIV engagement, then adding the values together to generate a single continuous score. These composite scores will be analyzed as exploratory outcomes, included as covariates in models predicting mental health outcomes, and used to test for interaction effects with intervention group to explore potential moderation.For HIV treatment engagement (among participants living with HIV), the following indicators will be composited into a single score:◦ Self-reported clinic attendance;◦ ART initiation and adherence;◦ HIV viral load documentation;◦ HIV treatment self-efficacy (via HIV-SE).◦ Each indicator will be scored and summed to create an overall treatment engagement score.◦ Higher scores reflect stronger engagement in HIV care.For HIV prevention engagement (among HIV-negative or status-unknown participants), the following indicators will be composited:◦ Consistent condom use;◦ PrEP uptake or readiness;◦ Reduction in HIV risk behaviors (via WAF);◦ HIV prevention self-efficacy/readiness (via HPRM).◦ Higher scores reflect stronger engagement in HIV prevention strategies.

*Moderation and mediation analyses (exploratory)*: Post hoc exploratory analyses will assess whether changes in mental health outcomes mediate or moderate the intervention’s effects on HIV-related outcomes. Mental health change scores will be calculated separately for each follow-up period (i.e., 3 months and 6 months post-intervention) by subtracting baseline values from the respective follow-up values. This will allow us to assess both short-term and sustained mental health changes and explore their relationship with HIV-related outcomes over time.Mediation: We will test whether changes in CMD symptoms (SSQ-14), depression (PHQ-9), anxiety (GAD-7), or PTSD (CPSS) symptoms help explain (mediate) observed changes in HIV prevention or treatment outcomes using causal mediation models.Moderation: We will include interaction terms between changes in mental health symptoms and intervention group to assess whether the impact of the intervention on HIV outcomes differs depending on mental health changes. Additionally, we will explore whether baseline levels of early adversity (measured by the Adverse Childhood Experiences International Questionnaire; ACE-IQ) [64], social support (measured by the Oslo social support scale; OSSS-3) [66], and coping self-efficacy (measured by the Coping Self-Efficacy scale; CSE) [65] moderate the relationship between the intervention and mental health or HIV outcomes.

*Adjustment variables and stratified analyses:* HIV status (positive vs. negative/unknown) will be included as a covariate in pooled models to adjust for baseline differences. Stratified analyses by HIV status will be considered if each group has a sufficient sample size to support reliable subgroup modeling (e.g., ≥ 40 participants per group). Given the small overall sample size (*N* = 90, accounting for 30% attrition), such stratified analyses may be underpowered and are therefore considered exploratory and hypothesis-generating only. All models will follow an intention-to-treat (ITT) framework, and statistical significance will be assessed at a two-sided *α* = 0.05, with 95% confidence intervals reported. Non-adherence will be handled by analyzing all participants as randomized (ITT); we will also run a pre-specified per-protocol sensitivity analysis defined as completion of ≥ 4/6 sessions and no major protocol deviations. Missing data will be addressed using mixed-effects models, which provide valid estimates under missing-at-random assumptions.

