*Mpata Yathu*has been specifically tailored for AGYW aged 15 to 24 who have experienced GBV and are living with or at risk for HIV. Using principles of Community-Partnered Participatory Research (CPPR), we relied on community partner feedback to guide the adaptation process [34, 35]. In CPPR, community partners are individuals and organizations that represent and serve the community, bringing local knowledge, lived experience, and leadership to shape and guide all phases of the research [34]. The process of developing the adaptation is described elsewhere. This adaptation maintains the core principles of the original Friendship Bench intervention—namely, structured PST that supports participants in identifying and addressing personal problems—but introduces several critical modifications. These include training lay counselors on how to navigate GBV-related conversations and referrals among their clients, integrating trauma-informed and survivor-centered approaches into counseling delivery and practice (i.e., allowing clients to choose their counselor), and situating the delivery within church spaces to leverage the social authority and reach of religious institutions in Zambia. Church-based delivery is intended to reduce barriers to access by situating the intervention within trusted and familiar community environments, while also capitalizing on the role of churches as influential actors in shaping norms related to gender, mental health, and HIV.

Unlike the original model which deploys “grandmothers” to deliver the intervention, *Mpata Yathu* will be implemented by lay counselors with diverse backgrounds and age ranges (e.g., young adults, middle-aged, pastors, schoolteachers, students, peer navigators, etc.) and the clients will choose their counselor in the order of their preference. Allowing choice by the clients was intended as part of our trauma-informed, survivor-centered approach. Trained lay counselors will deliver the intervention within church settings following an intensive training program that includes PST techniques, ethical protocols, and guidance on supporting GBV survivors. Each participant will be offered six weekly sessions lasting approximately 45–60 min. In addition to PST delivery, the intervention includes structured referral pathways to mental health/psychiatric support, HIV services, and GBV response mechanisms, ensuring participants receive appropriate and timely care beyond the sessions themselves.

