Lastly, we will qualitatively assess barriers and facilitators of Friendship Bench implementation via semi-structured interviews on intervention experiences among study participants and lay counselors using relevant domains and constructs from the Consolidated Framework for Implementation Research (CFIR) [70], and the modified CFIR for LMICs [71]. We are hoping that capturing barriers and facilitators would also allow us to qualitatively assess satisfaction and burden (i.e., risks and benefits associated with participation among counselors and clients). We will qualitatively assess the feasibility and acceptability of the intervention through semi-structured interviews with both participants and lay counselors. All lay counselors who delivered the intervention (up to 12 total) will be invited to voluntarily participate in an interview. Additionally, we will conduct up to 15 interviews with participants from each study arm (intervention and delayed control group) to gather diverse perspectives on the intervention experience. To accommodate participants who are not fluent or comfortable communicating in English, interviews will be conducted in local languages (e.g., Nyanja or Bemba) by trained bilingual interviewers. All audio recordings will be transcribed and then translated into English (if applicable) for analysis. To ensure accuracy and cultural validity, a subset of transcripts will undergo back-translation and review by the research team.

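### At 3 months the intervention arm is nested within at most 12 counselors, but the primary model and the 80% power both treat all women as independent

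*Protocol article*

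**What the plan says.** Women are randomised individually, 1:1. The intervention arm is offered up to six one-to-one sessions in months 0 to 3. The waitlist arm has usual care in that period and is offered the sessions in months 3 to 6 (Study design). The between-group comparison is made at 3 months (Study outcomes; Power analysis).

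The Implementation outcomes section gives the number of counselors, in describing the interviews: "All lay counselors who delivered the intervention (up to 12 total". They are of mixed background and age, and "the clients will choose their counselor in the order of their preference" (Description of the intervention).

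The Power analysis section states: "With the proposed sample size of 126 participants (63 per arm", "using a two-sided alpha level of 0.05", "the study will have 80% power to detect a medium effect size", namely d = 0.5. This is raised to 90 per arm for 30% attrition.

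The primary model (Quantitative data analysis) has fixed effects for time, group and their interaction, and one random effect: "A random intercept for participants to account for within-subject correlation from repeated measures". HIV status is added later as a covariate. The article gives no counselor term, cluster-robust variance, ICC or design effect.

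**The concern.** At the primary endpoint this is a partially nested design. Women in the intervention arm share counselors; women on the waitlist share none. If some counselors get better results than others, outcomes within a caseload are correlated and the treated-arm mean varies more than independent data would.

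A participant random intercept handles the correlation between one woman's repeated scores. It does nothing for correlation between women seen by the same counselor. The model would then report too narrow an interval for the only outcome on which the trial is powered, and the stated power would rest on an unstated ICC of zero.

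The protocol itself treats counselor performance as variable: it plans a fidelity checklist, weekly supervision and early review of recorded sessions to give feedback.

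**Working it through.** **Inputs from the article.** d = 0.5 with SD 1; two-sided alpha 0.05; 63 analysed and 90 enrolled per arm; at most 12 counselors. The average caseload is therefore m = 63/12 = 5.25, the smallest possible average, because 12 is a maximum.

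**Assumptions, not in the article.** Counselor ICC of 0.02, 0.05 or 0.10; coefficient of variation (CV) of caseload of 0 (equal) or 0.6.

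**Step 1: the plan's own figures.** n = 2(1.960 + 0.842)²/0.5² = 62.8, so 63 per arm; power at 63 is 80.1%; 63/0.70 = 90. All three reproduce under independence, so they contain no hidden allowance for clustering.

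**Step 2: clustering in the treated arm only.**
- Design effect: DE = 1 + [(1 + CV²)m − 1] × ICC
- True SE = √[(DE + 1)/n]; SE from the planned model = √(2/n) = √(2/63) = 0.178
- Power of a correctly clustered test = Φ(0.5/SE − 1.96)
- Type I error of the unclustered test = 2Φ(−1.96 × 0.178/SE)

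Worked case, ICC 0.05, equal caseloads: DE = 1 + 4.25 × 0.05 = 1.2125; SE = √(2.2125/63) = 0.187; power = Φ(2.668 − 1.960) = 76.1%; type I error = 2Φ(−1.96/1.052) = 6.2%.

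| ICC | CV | DE | SE / planned SE | Power, clustered test | Type I error, unclustered test |
|---|---|---|---|---|---|
| 0.02 | 0 | 1.085 | 1.02 | 78.5% | 5.5% |
| 0.05 | 0 | 1.21 | 1.05 | 76.1% | 6.2% |
| 0.10 | 0 | 1.43 | 1.10 | 72.2% | 7.5% |
| 0.02 | 0.6 | 1.12 | 1.03 | 77.8% | 5.7% |
| 0.05 | 0.6 | 1.31 | 1.07 | 74.3% | 6.8% |
| 0.10 | 0.6 | 1.61 | 1.14 | 69.0% | 8.6% |

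These use the normal approximation. With a t reference and 11 degrees of freedom for the counselor part, the equal-caseload powers are 76.2%, 73.5% and 69.3%.

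**Step 3: fewer counselors.** With 8 equal caseloads of 7.88, power is 73.6% at ICC 0.05 and 67.8% at ICC 0.10.

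**Step 4: no attrition.** With 90 analysed per arm, m = 90/12 = 7.5. With equal caseloads, power is 90.2%, 87.5% and 83.0% at the three ICCs. Type I error of the unclustered test is 5.7%, 6.9% and 8.9%, because larger caseloads raise the design effect.

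**Step 5: completers needed for 80% power (12 equal caseloads).** 66, 71 and 81 per arm. At 30% attrition that is 95, 102 and 116 enrolled per arm, against the planned 90.

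**The case against.** Several counterarguments stand in part.

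- **The size is assumed.** The article gives no ICC and no caseload distribution. At ICC 0.02 with equal caseloads the power loss is under 2 points. Only the direction, for any ICC above zero, is certain.
- **Uneven caseloads are not established.** A reader might infer that client choice makes caseloads uneven. A ranked preference is also compatible with allocation limited by capacity, and the article does not say which applies. The CV of 0.6 illustrates a possibility.
- **The two harms do not occur together.** A reader might infer that the plan as written has only 74% power. That figure belongs to the clustered test at ICC 0.05 and CV 0.6. The unclustered test has power Φ[(0.5 − 1.96 × 0.178)/SE], about 78.5% in that setting and 79% with equal caseloads. Its main cost is type I error.
- **The type I figure needs a particular null.** If therapy changes nothing for anyone, individual randomisation protects the comparison, however women sort themselves among counselors. The inflation applies when counselor effects vary around an average of zero. That null is relevant here, since the trial is meant to inform larger ones with other counselors.
- **Retention or baseline data may restore power.** Both may, but neither corrects the standard error. For example, assume a baseline to follow-up correlation of 0.7 and a change-based contrast. At ICC 0.05 with equal caseloads, SE = √[(0.6 + 0.2125 + 0.6)/63] = 0.150, below the 0.178 behind the 80%, so power is ample. The unclustered test's type I error is still 7.1% (9.2% at ICC 0.10).
- **Detail may sit in an analysis plan.** A small-sample correction could. But the article itself fixes the power figure and lists the model terms, and both assume independence.

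**Conclusion.** The point holds as a conditional one. At 3 months only the intervention arm is nested within counselors, and neither the primary model nor the power statement allows for it. For any positive counselor ICC the planned standard error is too small and the 80% is optimistic.

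With 63 analysed per arm and 12 counselors, a clustered test has about 72% to 78.5% power for ICC 0.10 to 0.02 with equal caseloads, or about 69% to 78% with a caseload CV of 0.6. The unclustered test's type I error is about 5.5% to 7.5%, or 5.7% to 8.6%, under the zero-average null. All of this rests on assumed ICCs.

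The documents do not support the reading that true power is one particular lower figure, or that the error rate exceeds 5% under every null. Nor do they show that the trial must be too small: with full retention and equal caseloads, power stays above 80% up to ICC 0.10. The sample size arithmetic itself is correct.

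**What to change.** **Quantitative data analysis.** Add a counselor random effect that acts in the intervention arm only (a partially nested mixed model), with Satterthwaite or Kenward-Roger degrees of freedom. Treat each waitlist woman, and each intervention-arm woman who attends no session, as her own unit, so that the intention-to-treat set stays complete.

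**Data collection.** State that the counselor is recorded for each participant. The article says that counselors' logs track sessions completed and that counselors write post-session notes. It does not say that counselor identity is captured, so this should not be assumed.

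**Power analysis.** State that 80% assumes no counselor clustering, and give power over an assumed ICC range: about 72% to 78% for ICC 0.10 to 0.02 with 12 equal caseloads and 63 analysed per arm. Alternatively, show that the baseline-adjusted analysis recovers the loss. A single replacement figure should not be written in, because it would carry an ICC that the trial has not justified.

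**Cost.** A slightly wider interval, a less favourable stated power and one more recorded item. No extra participants or visits are needed if the change is made before analysis.
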